## Variables

The movement during the rVMA task will be described by the calculated movement time (MT, ms), travel distance (TD, cm) and reaction time (RT, ms) variables. RT will be defined as the time between target appearance and movement onset. Movement output error will be measured through the initial directional error (IDE, deg) and root mean square error (RMSE, cm) variables (Figure 5). IDE will be calculated as the absolute angular difference between the ideal trajectory, a linear vector from the center to the target, and the early real trajectory, defined by the linear vector from the center to the green dot position at the time of 80 ms after movement onset. IDE will be used as a measure of the rotation adaptation or motor consolidation avoiding the possible trajectory correction through perceptual feedback (Contreras-Vidal et al., 2005; Ferrer-[name] et al., 2018, 2017). RMSE will be calculated to represent the straightness of the movement between the ideal trajectory and the real joystick trajectory following the procedure described in Contreras-Vidal et al. (2005):

$$RMSE = \sqrt{\sum_{i=1}^N [(x_1 - x_2)^2 + (y_1 - y_2)^2] \frac{1}{N}}$$

where  $(x_1, y_1)$  and  $(x_2, y_2)$  are the coordinates of the real and ideal trajectory, respectively, and  $N$  is the number of points in the path. Movement straightness (i.e., RMSE) includes the initial deviation from the ideal trajectory (IDE) and the remaining movement trajectory, which could be corrected using perceptual feedback. All these variables will be calculated for each set (baseline, adaptation, RT1h, RT24h, and RT7d). Considering the large inter-subject variability usually presented by children, computed mean adaptation and retention variables will be normalized by subtracting the participant's mean baseline values.

It is proposed that DCD groups will show more variability than their TD peers (King, Haring, Oliveira, & Clark, 2011; Roche et al., 2016; Smits-Engelsman & Wilson, 2013). Inter-trial variability will be calculated via SD for all performance variables in the rVMA (MT, MT-SD, TD, TD-SDRT, RT-SD, IDE, IDE-SD, RMSE, and RMSE-SD) to characterize the groups.

During the adaptation set, data typically present an initial rapid-error decay followed by a slower decline. As it has been seen in other studies (Ferrer-[name] et al., 2018, 2017; Krakauer, Ghez, & Ghilardi, 2005), these data from adaptations seem to be best fitted by a double exponential function:

$$y = a * e^{b*x} - c * e^{d*x}$$

where  $y$  is the error (epoch's mean),  $x$  is the epoch number and  $a$ ,  $b$ ,  $c$  and  $d$  are parameters. The initial rate of learning (RL) will be computed, as described in Coats (2014), as the first derivative of the first half of the function and evaluated at epoch 1 for both error variables IDE (RL-IDE) and RMSE (RL-RMSE). All individual exponential functions will be visually inspected for a plateau to assess that learning is achieved.

Progress towards increasingly skilled performance consists of the acquisition and stabilization of more effective movement patterns (Vereijken, Van Emmerik, Bongardt, Beek, & Newell, 1997). Inter-trial variability could be used to assess the stabilization level of the task. High values of variability are related to an early learning stage that explores new solutions for the task while low values of variability are associated with more skilled performers showing stable executions. Changes in variability across epochs in the acquisition set (i.e., rate of variability, RV) for both error variables (RV-IDE-SD and RV-RMSE-SD) will be also computed.

Normalized changes in concentration levels of hemodynamic variables during the different sets will be analyzed. Neural activation of each cortical area will be expressed as an increase of  $[O_2Hb]$  (also of  $CMRO_2$  and CBF in the pilot study) and a decrease in  $[HHb]$  (Mandrick et al., 2013). Qualitative analysis of the changes in these variables across trials will be performed to establish differences in hemodynamic patterns. Average and SD of the hemodynamic variables for each set will be calculated.

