Children with DCD showed difficulties in motor adaptation (Bo & Lee, 2013). The internal model generation capacity in children with DCD has been studied using rVMA tasks (Kagerer, Bo, Contreras-Vidal, & Clark, 2004; Kagerer, Contreras-Vidal, Bo, & Clark, 2006; King, Kagerer, Harring, Contreras-Vidal, & Clark, 2011). Kagerer et al. (2004) exposed children with and without DCD to a novel visuomotor task. In the baseline condition (no rotation), DCD children were more variable and showed lower accuracy than TD children. When the visual feedback was rotated 45° in relation to their hand movements, children with DCD did not show observable after-effects compared to TD children. That is, DCD children did not realize that the alteration was removed indicating a weak modification of their internal model during the adaptation phase. The authors suggested that DCD children had a poorly defined visuomotor internal model in the baseline condition (i.e., larger variability) that made difficult to detect differences if they did not overpass this variability level. A follow up study conducted by Kagerer et al. (2006) indicated that both groups (DCD and TD) adapted to the visuomotor perturbation when it was suddenly introduced (i.e., 60° perturbation) but adaptation in DCD children was smaller than in TD with similar number of trials. Conversely, if the perturbation was gradually presented (i.e., increments of 10° of perturbation to achieve 60°), DCD children did not appear to be able to use the small differences in perceptive signals to adapt their internal model. These results seem to indicate that: (1) DCD children may be able to adapt their internal model but they will need enough sensory discrimination to generate error feedback (i.e, the alteration must be larger than variability); and (2) the rate learning of DCD children may be slower than TD children (Gomez & Sirigu, 2015) . Given the known role of the cerebellum in providing an error signal necessary for updating the sensorimotor mapping in response to a gradual visuomotor distortion, findings from Kagerer et al. (2006) implicated compromised cerebellar function in children with DCD (H. Imamizu, Kuroda, Miyauchi, Yoshioka, & Kawato, 2003; H. Imamizu, Kuroda, Yoshioka, & Kawato, 2004; Hiroshi Imamizu et al., 2000; Zwicker et al., 2010). Additionally, suboptimal parietal and cerebellar networks in DCD due to poor visual spatial integration for online movement controls and poor motor

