At the start of session 2, participants will be familiarized with the rVMA protocol (familiarization set) by performing 20 trials of non-rotated ( $0^\circ$ ) practice trials. Afterwards, a non-rotated baseline condition set (104 trials) will be performed. After the baseline set, the EX groups (i.e., EX-DCD and EX-TD) will perform a 13-min iE session while the CON groups (i.e., CON-DCD and CON-TD) will rest the same period of time reading or holding a conversation, no additional exercise or musical activity will be permitted. Next, all participants will do an adaptation set (312 trials) in the rVMA task, with a clockwise rotation of  $60^\circ$  applied to the cardinal coordinates of the cursor movement. At one hour after the end of the adaptation set, all participants will perform a  $60^\circ$  clockwise retention set (short-term retention, RT1h, 104 trials). At the end of session 2, all participants will perform a memory game with the cards they collected during the 20mSRT and potentially the iE.

Sessions 3 and 4 will occur 24 h and 7 days from the end of the adaptation set. In each session, participants will perform a  $60^\circ$  clockwise rotated retention set (mid and long term retentions, RT24h, and RT7d respectively, 104 trials each).

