A list of the principal tasks related to the research objectives are presented indicating members of the group involved. Critical tasks that could alter the expected timing (underlined) are related to the accessibility of the sample and DCD children detection.

- **Task 1.** Participant recruitment
  - Task1.1. Participant recruitment. Investigators involved: PI1, WT3, WT4. Duration: M1-36.
- **Task 2.** Objective 1
  - Task 2.1. Collection of participant's characterization data, including: Health status (PARQ), physical activity engagement (PAQ-C), academic and daily living activities performance (MABC-2 checklist), possible comorbidities report, regular medication intakes, possible psychosocial problems (Conners CBRS), exclusion criteria related-data, and the family-related information. Investigators involved: PI1, PI2, WT3. Duration: M2-40.

- Task 2.2. Intelligence quotient data collection using the Test of on-verbal intelligence version 4 (TONI-4). Investigators involved: PI1, PI2, WT3. Duration: M2-40.
- Task 2.3. Motor coordination data collection using the Movement assessment battery for children – second edition (MABC-2). Investigators involved: PI1, PI2, WT3. Duration: M2-40.
- Task 2.4. Participant's anthropometric data collection. Investigators involved: PI1, PI2, WT3. Duration: M2-40.
- Task 2.5. Estimation of participant's VO2max via the 20-meter shuttle run test (20mSRT). Investigators involved: PI1, PI2, WT3. Duration: M2-40.
- Task 2.6 Exercise intervention execution and motor learning (rotational visuomotor adaptation task) behavioral data collection. Investigators involved: PI1, PI2, RT1, WT3, WT4. Duration: M2-40.
- Task 2.7. Reduce data and carry bio-statistical procedures. Investigators involved: PI1, PI2, RT1, WT1, WT2, WT3. Duration: M7-45.
- Task 2.8. Produce results and disseminate according to dissemination plan. Investigators involved: PI1, PI2, RT1, WT1, WT2, WT3. Duration: M14-48.
- **Task 3.** Objective 2 and 3
  - Task 3.1. Brain activity data acquisition under resting state and baseline execution of the motor task (rotational visuomotor adaptation task without deviation of hand movements). Investigators involved: PI1, RT1, WT3, WT4. Duration: M2-40.
  - Task 3.2. Brain activity data collection during the acquisition and retention of the new motor skill (rotational visuomotor adaptation task with hand movements deviated 60 degrees clockwise). Investigators involved: PI1, PI2, RT1, WT3, WT4. Duration: M2-40.

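### Subtracting a 0-degree baseline from an absolute directional error biases the DCD–TD learning comparison towards the noisier DCD group, and can mask or possibly reverse a true deficit

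*Protocol*

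**What the plan says.** The Variables section of the protocol fixes the scale: "IDE will be calculated as the absolute angular difference between the ideal trajectory" and the early movement vector, taken 80 ms after movement onset. It then fixes the normalisation: "computed mean adaptation and retention variables will be normalized by subtracting the participant's mean baseline values". No signed IDE is defined anywhere.

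Baseline and learning phases differ in rotation. In Experimental protocol, "a non-rotated baseline condition set (104 trials) will be performed" before the exercise or rest period. Adaptation and all three retention sets are run rotated, described in the work plan (Task 3.2) as "rotational visuomotor adaptation task with hand movements deviated 60 degrees clockwise".

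The protocol expects the cohorts to differ in scatter. Motor Learning and DCD reports from an earlier study: "In the baseline condition (no rotation), DCD children were more variable and showed lower accuracy than TD children". Variables adds for this trial: "It is proposed that DCD groups will show more variability than their TD peers". Inter-trial SDs are to be derived for all performance variables, and their change across adaptation epochs "for both error variables (RV-IDE-SD and RV-RMSE-SD) will be also computed".

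Under Statistical analysis, CON-DCD and CON-TD (O1.2) are compared by independent t-test in adaptation and by 2 x 3 repeated-measures ANOVA in retention. The exercise question (O1.3) uses 2 x 2 and 2 x 2 x 3 ANOVAs.

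**The concern.** An absolute error mixes two quantities: how far a child's movements are off on average, and how much they scatter. The mix depends on the size of the average error. At 0 degrees a child without directional bias still has a positive mean absolute IDE, made up of scatter. At 60 degrees, early in learning, mean absolute IDE is nearly all residual error. Subtracting the first from the second is therefore not a like-for-like correction, and it costs more points in a child who scatters more.

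Because DCD children are expected to scatter more, the normalised score flatters them. H1 predicts worse learning and consolidation in DCD, so the bias works against the hypothesis. IDE is one of the two error variables by which learning is judged, and the sample-size paragraph draws its effect sizes from IDE data.

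Taking the absolute value also distorts variability. Folding the distribution at zero compresses its spread when mean error is small, so IDE-SD can fall during adaptation while the child's real scatter stays the same. The protocol would read that fall as stabilisation.

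**Working it through.** **Inputs.** From the protocol: absolute IDE, subtraction of the child's baseline mean, 0 degrees at baseline, 60 degrees afterwards, more scatter expected in DCD, 30 children per cell. The protocol gives neither within-child SDs nor expected residual errors, so there is no figure of its own to reproduce. Assumed here: TD/DCD trial SDs of 6/10, 8/12, 10/15, 12/20 and 10/20 degrees; residual error from 0 to 60 degrees; normal trial errors; no directional bias at baseline.

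**Formula.** For residual error m and within-child SD s, mean absolute error is

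E(m, s) = s·√(2/π)·exp(−m²/2s²) + m·(1 − 2Φ(−m/s)).

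At m = 0 this is 0.80·s. For m well above s it is about m. The normalised score is E(m, s) − E(0, s).

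**One case in full.** SDs 10/15, both groups truly at 20 degrees:
- TD: 20.17 − 7.98 = 12.19
- DCD: 21.27 − 11.97 = 9.30
- DCD − TD = −2.89, although the true difference is 0.

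**Normalised DCD − TD at equal true residual (degrees; negative means DCD looks better).**

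| SD TD/DCD | m = 0 | 10 | 20 | 30 | 60 |
|---|---|---|---|---|---|
| 6/10 | 0.00 | −1.76 | −3.02 | −3.18 | −3.19 |
| 8/12 | 0.00 | −1.28 | −2.75 | −3.14 | −3.19 |
| 10/15 | 0.00 | −1.12 | −2.89 | −3.74 | −3.99 |
| 12/20 | 0.00 | −1.19 | −3.53 | −5.26 | −6.37 |
| 10/20 | 0.00 | −1.73 | −4.82 | −6.81 | −7.96 |

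The limit at large m is 0.80·(SD_DCD − SD_TD).

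**Normalised DCD − TD when DCD is truly 5 degrees worse.**

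| SD TD/DCD | TD residual 0 | 10 | 20 | 30 |
|---|---|---|---|---|
| 6/10 | 0.98 | 2.16 | 1.85 | 1.81 |
| 8/12 | 0.82 | 2.21 | 1.94 | 1.82 |
| 10/15 | 0.66 | 1.84 | 1.44 | 1.10 |
| 12/20 | 0.50 | 1.14 | 0.16 | −0.78 |
| 10/20 | 0.50 | 0.60 | −1.13 | −2.34 |

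The sign has turned by a TD residual of 25 for 12/20 (−0.37) and of 15 for 10/20 (−0.23). It does not turn for the three narrower pairs.

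**Effect on the t-test.** Simulation with 30 per group, 104 trials and 1000 replicates, assuming a between-child SD of m of 8 degrees, a baseline-bias SD of 3 degrees and a log-SD of s of 0.2:
- No true difference: the test significantly favoured DCD in 19% of replicates (m = 15, SDs 8/12) and in 67% (m = 20, SDs 10/20). Signed IDE minus signed baseline rejected in 4–6%, two-sided.
- True 15 against 20 degrees, SDs 8/12: power 19% under the protocol's rule, 56% signed.
- True 20 against 30 degrees, SDs 8/12: 90% against 99.5%.

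**SD of absolute IDE.** √(m² + s² − E²), as a multiple of s: 0.60 at m = 0, 0.80 at m = s, 0.965 at m = 2s, about 1.0 beyond that.

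**Exercise effect.** The baseline precedes randomised exercise, so its subtraction cancels in expectation from EX − CON within a cohort. The absolute value itself does not cancel. A true gain from 15 to 10 degrees appears as 3.92 in TD and 2.97 in DCD (10/15), or 3.49 and 2.33 (12/20). From 30 to 25 degrees, 10/15 gives 4.97 and 4.66.

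**The case against.** Several points in the plan's favour stand.

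- A reader might infer that scatter is absent under rotation. It is present; it only stops adding to the mean once the residual exceeds it. Near full adaptation the subtraction is close to right for equal groups. The protocol expects error to decay rapidly and checks for a plateau, so late residuals may be small.
- A reader might infer that the DCD deficit will be reversed. That needs a true deficit below roughly 0.8·(SD_DCD − SD_TD) with substantial residual error. The documents give no SDs, so reversal is a possibility only.
- A reader might infer that the randomised exercise result is spoiled. The subtraction leaves EX − CON and Group x Exercise unbiased in expectation. RL-IDE is a derivative, and a constant does not change it.
- Baseline scatter is diluted if children have directional bias at 0 degrees. With 10 degrees of bias in both groups (SDs 10/15), the distortion at residual 30 falls from 3.7 to 2.6 degrees.
- Statistical analysis allows variables with initial group differences to become ANOVA covariates. Entering baseline would replace the fixed subtraction by an estimated coefficient. That step is discretionary, and no covariate is stated for the O1.2 adaptation t-test.
- The full 40% fall in the SD of absolute IDE requires complete adaptation, which is where the equal-residual subtraction bias is zero. The two distortions peak at opposite ends of learning.

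These points narrow the scope. They do not remove the bias in O1.2: at small residuals a true 5-degree deficit is still cut to about 2 degrees or less.

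**Conclusion.** Wrong as written; should be fixed before analysis. The results exposed are O1.2 and the Group main effect on normalised IDE, together with IDE-SD and RV-IDE-SD. If DCD children scatter more and residual error remains, the normalised comparison understates their deficit. It can mask a moderate deficit and may reverse it where the SD gap is wide. A large deficit survives.

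The direction follows from the protocol's own statements. The size rests on the assumed SDs and on little directional bias at baseline. The O1.3 contrasts are not biased by the subtraction. When residuals are small, though, the absolute value shrinks true exercise effects, more so in the noisier group, which bears on the H1 claim that exercise narrows the gap. RMSE is also non-negative and baseline-subtracted, so the same caution applies; its size was not worked out.

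**What to change.** In the Variables section:

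1. Define IDE as a signed angle, positive in the direction of the imposed rotation.
2. Use mean signed IDE minus mean signed baseline as the adaptation and retention outcome.
3. Compute IDE-SD and RV-IDE-SD from signed trial values. Report IDE-SD beside the signed mean, because opposite errors can cancel and a scattered child could otherwise look adapted.
4. Keep absolute IDE as a descriptive secondary measure only. Dropping the subtraction is no cure: at zero residual, raw absolute IDE makes DCD look worse by 11.97 − 7.98 = 3.99 degrees (SDs 10/15). It should not carry DCD–TD inference with or without subtraction.
5. State how baseline-subtracted RMSE will be interpreted between cohorts.

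The cost is a sign in the data-reduction code and a few sentences. The x-y coordinates are already recorded. The price is slightly less direct comparability with earlier studies, which the descriptive absolute IDE largely covers.

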In order to examine the combined effect of acute exercise and learning on children's brain activity, widely used neuroimaging techniques are either too expensive, or do not allow for in-situ assessment (i.e., same location where learning is occurring, in our case, children's school). Optical technologies have been utilized and suggested as potential and promising tools to fully study the alterations of the brain networks. Perhaps most importantly, the features of the new technological approach (non-invasive, quantitative, safe, inexpensive and portable) and the characterization of brain activity using fNIRS will allow us to conduct studies in-situ (i.e., children's school) with robust results, including estimation of what brain areas are more or less activated while learning in children with DCD. In addition, combination of two optical techniques, fNIRS and DCS, has the potential to add new reliable information of the children's brain activity during learning which open the door to conduct a pilot study to verify this potential. This knowledge is hypothesized to assist in the design of better, more targeted interventions. In addition, exercise benefits in learning, if confirmed in this population, could also be integrated as part of effective educational interventions for children with DCD. Our research hypotheses are arranged around these concepts.

- H1: Children with DCD will show worse motor learning (slower movements, more variability, slower rate of learning, and worse consolidation) than

typically develop (TD) children when facing a rotational visuomotor adaptation task (rVMA). Performing an acute intense exercise bout before rVMA will improve consolidation in TD and DCD children. In addition, exercise will narrow the gap between children with DCD and children with TD. Based on the null exercise effect on adaptation previously found in TD children, we have no predictions for DCD children.

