We will compare the mean baseline value for each rVMA and brain hemodynamics variables with ANOVAs to evaluate baseline performance across the four groups. Differences between the CON-DCD and CON-TD children groups (O1.2 and O2.1) on the motor learning (adaptation and retention phases) will be explored using independent t-tests in the adaptation set, while 2 (Group) x 3 (Time) ANOVAs with repeated measures will be used to analyze differences in the retention phases. Focusing on the effects of exercise (O1.3 and O2.2), possible differences in the adaptation set will be contrasted by 2 (Group) x 2 (Exercise) ANOVAs and retention tests will be analyzed by 2 (Group) x 2 (Exercise) x 3 (Time) ANOVAs with repeated measures. Association of the changes in brain activation variables with changes occurred in the rVMA variables will be explored using bivariate correlations and multivariate correlations (O2.3). Usability and additional information provided by fNIRS and fDCS will be evaluated qualitatively and contrasted brain activity levels obtained from both technologies using t-test and ANOVAs (adaptation: t-test (Technology); retention tests: 2 (Technology) x 3 (Time) ANOVAs) (O3).

Before any statistical test normality distribution will be tested for all variables via exploration of histograms, Q-Q plots and with the Shapiro-Wilk's normality test. When the normality assumption failed, variable transformation or non-parametric alternative tests will be adequately conducted. In all ANOVAs Greenhouse-Geisser sphericity-corrected values will be used when appropriate. Variables with initial group differences and significantly correlated with the dependent variable will be considered as potential covariates in the ANOVA analyses. Bonferroni *post hoc* analyses will be performed if significant differences are found. In addition, the effect size will be calculated using  $\eta^2p$  (0.01 small, 0.06 medium, 0.14 large effect). Statistical significance was set at  $p < 0.05$  for all analyses.

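### Retention is scored against the unrotated baseline only, so the DCD versus TD main effect on retention cannot separate incomplete learning from poorer consolidation

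*Protocol*

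**What the plan says.** Protocol, Variables, defines the scores: "computed mean adaptation and retention variables will be normalized by subtracting" each child's own baseline mean. The baseline set is unrotated and is done before exercise or rest and before any rotation (Experimental protocol: "condition set (104 trials) will be performed"). The same error score serves both learning phases: "IDE will be used as a measure of the rotation adaptation or motor consolidation".

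Protocol, Statistical analysis, gives the tests. For DCD versus TD in the control groups (O1.2), 2 x 3 "ANOVAs with repeated measures will be used to analyze differences in the retention phases". For exercise (O1.3), "retention tests will be analyzed by 2 (Group) x 2 (Exercise) x 3 (Time) ANOVAs with repeated measures". The three times are RT1h, RT24h and RT7d. Adaptation is tested separately, by t-test or a Group x Exercise ANOVA.

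The end-of-adaptation level is not subtracted, is not a level of Time and is not a named covariate. The covariate rule reads "Variables with initial group differences and significantly correlated with the dependent variable will be considered as potential covariates", which points to differences present at the start. From the fitted adaptation curve the plan takes an initial rate at epoch 1 and a visual check for a plateau. It extracts no final level.

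H1 lists "slower rate of learning, and worse consolidation" as distinct deficits in DCD, and O1 names adaptation and consolidation side by side.

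**The concern.** Consolidation is what is kept or lost between the end of practice and a later test. A retention score referenced only to unrotated performance also contains whatever error remained when practice stopped. A group that stopped at a higher error will show higher retention error even if it loses nothing overnight.

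The Introduction (Motor Learning and DCD) makes such a gap plausible: it describes earlier work in which children with DCD adapted less than TD children over a similar number of trials. Here every child gets the same 312 trials. The Protocol also presents consolidation in DCD as weakly examined and as a gap this project will fill. At stake is whether a DCD versus TD difference in retention may be called a consolidation deficit.

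A second, smaller issue is that each retention test is 104 trials at the same rotation, 13 epochs of 8. A whole-set mean therefore blends recall with relearning inside the test.

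**Working it through.** The plan states no figure that rests on this point, so there is none to reproduce.

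**Step 1: decompose the planned score.** For each child,

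(retention − baseline) = (end of adaptation − baseline) + (retention − end of adaptation).

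The first term is what remained unlearned. Only the second is offline change. The Group main effect tests the sum.

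**Step 2: which planned tests are affected.** The first term is the same at 1 h, 24 h and 7 d, so it cancels from differences between those times. Group x Time is therefore free of it, but reflects only change after 1 h. The Group main effect keeps it in full.

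**Step 3: size in SD units.** Inputs: 30 per cell and alpha .05 (Participants), taken as two-sided. Assumed: SD of end level 1, noise SD 0.5 per test, no offline loss in either group. The mean of three tests has SD √(1 + 0.25/3) = 1.04. A simulation of 4,000 trials gave these rates of a significant result:

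| End-level gap (SD) | Group main effect, retention − baseline | Retention − end of adaptation | Change 1 h to 7 d |
|---|---|---|---|
| 0 | 4.6% | 4.9% | 5.0% |
| 0.25 | 15.1% | 5.4% | 4.7% |
| 0.55 | 51.3% | 4.8% | 5.0% |
| 0.78 | 81.8% | 5.1% | 5.0% |

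The last two gaps borrow the numerical values of the Protocol's effect sizes; nothing says that the end-level gap is that large. Noncentral t agrees: at 0.78 the noncentrality is 0.78 / (1.04 × √(2/30)) = 2.90, power 81%.

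**Step 4: size in degrees.** Assumed: SD 12° at end of adaptation, correlation .7 with retention, and the same absolute loss in every child. Retention SD = 12/.7 = 17.1°, so the standard error of the group difference is 17.1 × √(2/30) = 4.43°.

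| Gap | Gap / SE | Rate of significant Group difference |
|---|---|---|
| 1.2° | 0.27 | 6% |
| 5° | 1.13 | 20% |
| 8° | 1.81 | 43% |
| 10° | 2.26 | 60% |

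**Step 5: when slower learning produces a gap.** Illustration: error = 60·exp(−x/τ) over 312/8 = 39 epochs.

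| τ (epochs) | Mean of adaptation set | Last epoch |
|---|---|---|
| 6 | 8.5° | 0.1° |
| 10 | 14.3° | 1.2° |
| 15 | 20.7° | 4.5° |
| 20 | 25.7° | 8.5° |

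A slower rate carries over only if adaptation is incomplete at 312 trials. The planned adaptation-set mean does not reveal this: between τ = 6 and τ = 10 it differs by 5.8°, the last epoch by 1.1°.

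**Step 6: does the change score settle it?** The 5% in Step 3 follows from assuming no loss, hence equal absolute loss, in every child. Suppose instead that each child loses the same fraction of what was learned (assumed: 60° start, TD end level 25°, DCD 35°, SDs as in Step 4). The noise SD is √(17.1² − 12²) = 12.2°. With a 30% loss, TD lose 0.3 × 35 = 10.5° and DCD 0.3 × 25 = 7.5°. The difference is 3°, with SD √(12.2² + 3.6²) = 12.8°, and the change score is significant in about 15% of trials, nearly always favouring DCD. At 20% and 50% loss the rates are about 10% and 29%. Children who learned less have less to lose.

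**The case against.** The strongest reply is that the problem is conditional. H1 predicts a slower rate, not a worse end level; 312 trials is long practice, and each fitted curve is inspected for a plateau. If both groups end level, nothing carries over, and a gap near 1° is harmless (6%). The cited earlier work gives no size for the gap in this task. This stands, and limits the claim to a risk. It does not remove it: a visual plateau check equates nothing, because a child can plateau at a high error.

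A reader might infer that slower learning in DCD is bound to be reported as worse consolidation, or that the retention analysis merely repeats the adaptation result. The documents support neither. The bias needs an end-level gap, and the planned Group x Time interaction tests differential change after 1 h without it.

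A reader might also infer that no exercise benefit on consolidation could be concluded. That goes too far. Exercise is randomised within cohort, adaptation is tested separately for an exercise effect, and H1 cites a null exercise effect on adaptation in TD children. For DCD it makes no prediction, so this contrast is less exposed rather than immune.

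Finally, Step 6 shows that a raw offline-change score has its own scale dependence. That stands, and is why it should not be the sole basis for claims.

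**Conclusion.** The point holds for the DCD versus TD consolidation claim in H1 and O1.2. The planned Group main effect on baseline-subtracted retention cannot separate incomplete learning from offline loss, and nothing else in the plan supplies the missing reference. With equal consolidation in both groups, the rate of a false consolidation finding runs from about 5% with no end-level gap to about 60% (10°) or 80% (0.78 SD) with a large one. These rates rest on assumed SDs, correlation and gaps; the Protocol gives none of them. The actual gap may be small.

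This is a cheap improvement that changes what the trial may conclude about consolidation. It does not invalidate the design, the randomised exercise comparison or the interaction tests.

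**What to change.** 1. For each child, compute mean error in the last adaptation epochs and in the first epochs of RT1h, RT24h and RT7d (for example the first two, 16 trials), fixing the number of epochs before analysis.
2. Analyse early-epoch retention relative to end-of-adaptation level (offline change) in the planned Group x Time and Group x Exercise x Time models.
3. Check scale dependence with end level as a covariate or with proportional retention, and report these beside the change score.
4. Keep the baseline-subtracted whole-set mean, labelled as overall retention performance.
5. Claim a DCD versus TD consolidation difference only if the analysis referenced to end of adaptation supports it.

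Cost: analysis wording only; the trials and 8-trial epochs already exist. Early-epoch means are noisier than 104-trial means. The covariate check has a limit too: with end level measured as noisily as in Step 3, its reliability is 1/(1 + 0.25) = 0.8, so about a fifth of any gap stays unadjusted (0.2 × 0.78 = 0.16 SD). Agreement between the analyses matters more than any one of them.
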